### *3.1.11. Data collection*

In February 2013 the TreatFOOD pilot study was carried out in the Province de Passoré, to assess the feasibility, acceptability and best practice of a range of the methodologies scheduled to be used in the main study. The methodologies evaluated were:

1. Anthropometry (weight, height/length, MUAC, crown-rump length, knee-heel length, skinfold thickness)
2. Physical activity using Actigraph accelerometers
3. Deuterium dilution technique for the assessment of lean body mass, including saliva sampling
4. Child development using an adapted version of the Malawi Development Assessment Tool

The procedures of the different methodologies mentioned above and described below have been adapted according to results of the pilot and therefore the study context.

Reports from the pilot study are available upon request.

### **Anthropometric measurements**

Weight, height, MUAC, crown-rump length, triceps skinfold, subscapular skinfold and knee-heel length will be measured for all children. All anthropometric measurements will be taken every second week during the intervention period except for height that will only be measured once a month. During the follow-up period, all measurements will be done monthly.

During the pilot study, the feasibility and acceptability of all measurements have been assessed. Furthermore the quality of training and measurements was assessed. The pilot study showed that all measurements were feasible in the study context and that procedures were well accepted by both mothers and children with few adjustments. Furthermore the quality of measurements of the pilot staff was acceptable after few days of training.

During the trial weight will be measured to the nearest 100 grams using an electronic scale that has a double weighing function. The double weighing function will enable young children to be on their mother's arm during weighing.. The scale will be regularly calibrated against a standard weight. Length or height and crown-rump length will be measured to the nearest 1mm using a standard UNICEF wooden measuring board. Children aged less than 24 months will be measured lying down and older children will be measured standing up. Knee-heel length will be measured to the nearest 0.1mm using an electronic hand-held

knemometer (*[name] KM et al, 1991*). MUAC will be measured on the left arm to the nearest 1 mm.

Triceps and subscapular skinfold thickness will be measured using a Harpenden skinfold caliper to the nearest 0.2 mm. All measurements will be recorded twice, except for knee-heel length, which will be measured five times. All measuring tools will be checked daily for accuracy and replaced if needed.

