### 3. Methods

#### 3.1. Effectiveness randomized controlled trial

##### 3.1.1. Study setting and study period

The trial will be conducted in selected district health centers “Centre de Santé et de Promotion Sociale” (CSPS) supported by ALIMA in the province of Passoré in the northern region of Burkina Faso. ALIMA’s program consists of support to district health structures for the management of severe acute malnutrition (SAM) in the District hospital of Yako and 53 CSPS in the province of Passoré. The trial will take place in five selected CSPS. Admission and follow-up take place 5 days a week on each site. The recruitment of children for the trial is expected to begin in August 2013. The intervention is planned for three months, with an additional three months of follow-up.

The prevalence of HIV among adults in Burkina Faso is 1.2 %. The estimated number of HIV infected children among our study participants is therefore likely to be very low.

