##### 3.1.2. Study population

Children will be eligible for inclusion if they fulfill the following criteria:

- weight-for-height z-score (WHZ)  $\geq -3$  and  $< -2$  (based on the WHO growth standard) or
- MUAC  $\geq 115$ mm and  $< 125$  mm
- 6 to 23 months of age,
- resident in the catchment area at the time of inclusion,
- whose parents/guardians have signed (or thumb-printed whenever illiterate) the informed consent.

---

 From 7.30am to 4 pm, all year long.

 UNAIDS 2009

 According to the workload, prior MUAC screening might be implemented.

 A local calendar of events will be piloted. If it does not appear suitable for inclusion based on age, children would be included based on a combination of event calendar and height.

Will be excluded:

- Children with severe acute malnutrition defined as a WHZ < -3, and/or a MUAC <115 mm, and/or bilateral pitting oedema. They will be referred to the health centres or Yako hospital for appropriate treatment,
- Children with medical complications requiring hospitalization,
- Children whose household plans to leave the catchment area in the next 6 months.
- Children with a hemoglobin concentration <4g/dl or with evidence of a decompensate anemia (eg, dyspnea, tachycardia...). These children will be transferred to the ITFC supported by ALIMA for appropriate treatment.
- Children who have been treated for SAM or who have been hospitalized in the last 2 months,
- Children with known allergy to milk, peanut, CSB and/or RUTF,
- Children with a severe disability limiting the possibility of investigations,
- Children enrolled in any other nutritional program or part of any other study conducted in the area.

Children with MAM who do not wish to participate in the study or who are excluded due to some of the above mentioned criteria, will be referred to the national supplementary nutritional program currently supported by WFP.

Appropriate free care, including referral to nutritional rehabilitation or pediatric care at Yako hospital (supported by ALIMA) when needed, will be offered to children who are non-eligible due to SAM or decompensated anemia.

Children will be recruited among children presenting spontaneously at the CSPA. All children taken to CSPA will be screened for eligibility. Furthermore active case finding within the community by community health workers supervised by ALIMA will be done.

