### **Tracer (Deuterium) dilution technique**

Body composition will be assessed at baseline and after 3 using the tracer dilution technique. In this technique, children will be weighed and a saliva sample will be collected with a cotton swab. Then, all children will be given a fixed standardized oral dose of liquid tracer (Deuterium, D2O), using 5 gr D2O diluted in 10 ml (~50% dilution) .. A second saliva sample will be taken after an equilibration time necessary for the tracer to evenly mix throughout the

body water. In healthy participants, equilibration is usually achieved after 2.5-4.5 hours and in general, children have faster water turnover than adults. However various disease states can influence water turnover and may delay equilibration (IAEA). Analysis of samples from the pilot study is ongoing and will determine the required equilibration time for children with MAM. During the equilibration time, children and caretakers will be provided with a meal and with activities (i.e knitting activities or others for the mothers and toys for the children). Health promotion sessions will also be conducted during this time.

The saliva sample will be analyzed for tracer distribution taking into account the volume of any fluid intake during the equilibration period. The concentration of the tracer in the saliva will allow estimating the total body water. Raw values for total body water will then be converted to lean mass measured in grams, using age-and sex-specific values for the hydration of lean tissue (Fomon SJ *et al*, 1982). The tracer enrichment of the saliva samples will be assessed using Fourier transform infrared (FTIR) spectrophotometry. Saliva samples will be analyzed at the IAEA Collaborating Centre, SJRI.

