### **Summary of changes to the statistical analysis plan:**

Compared to the statistical plan outlined in the protocol, we eventually decided to deviate on two issues:

1) Our primary outcome was fat-free mass accretion over three months, adjusted for length. We have not changed the primary outcome, but decided to do the length adjustment by dividing with length in meters squared, ie expressing fat-free mass accretion as an index. There are several reasons for this: First, we found that dividing by length in meters squared was the optimal adjustment. Second, since children are growing in length, then it is not enough to adjust for baseline length. Using fat-free mass index at both time points enable us to adjust for not only baseline length, but also changes in length over time.

2) We had initially planned to adjust for multiplicity, in case we had to compare 12 groups. However, while this reduces the risk of type 1 errors, it also increases the risk of type 2 errors. We therefore eventually followed standard practice of not adjusting p-values for reduced factorial model. In other words, for the pairwise comparisons within factors in the reduced models no multiplicity adjustments were applied.

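### Changing from lying to standing measurement at 24 months mixes a posture change into length gain and the fat-free mass index of children who turn two during the trial

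*Combined protocol and SAP*

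**What the plan says.** The posture rule is in section 3.1.11, Anthropometric measurements: "Children aged less than 24 months will be measured lying down and older children will be measured standing up". Its effect depends on three other statements.

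- Age at entry (section 3.1.2): "6 to 23 months of age".
- Duration (section 3.1.1): "The intervention is planned for three months, with an additional three months of follow-up".
- Repetition (section 3.1.11): during the intervention the text refers to "height that will only be measured once a month", and after it, "During the follow-up period, all measurements will be done monthly".

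Length enters the outcomes in several ways. Section 3.1.5 lists linear growth and a lean-mass increment in kg/cm as secondary outcomes. The summary of changes to the statistical analysis plan says that the authors "decided to do the length adjustment by dividing with length in meters squared" for the primary outcome, and explains: "Using fat-free mass index at both time points enable us to adjust for not only baseline length, but also changes in length over time".

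Lean mass itself is measured twice: "Body composition will be assessed at baseline and after 3 using the tracer dilution technique" (section 3.1.11; the missing unit is months, as Table 2 shows).

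The documents state no conversion between the two postures, no recording of posture, and no rule to keep a child in one posture.

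**The concern.** All eligible children are under 24 months at baseline and so are measured lying down. Among trial participants the standing clause can only apply to a child who turns 24 months after enrolment. Each time it applies, the measuring method changes within a child between two values that will be subtracted.

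If standing height reads shorter than lying length, the change has two effects in that child. Length gain is lowered by the full difference. Any index with length squared in the denominator is raised, because the follow-up denominator is too small. The second effect bears directly on the reason given for the index, which was to account for real changes in length over time. A kg/cm outcome would be affected in the same direction if it divides by length at each visit.

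At stake are the absolute mean changes for each group, which section 3.1.13 says will be presented, and any description of gains by age. Section 2.2 also sets an objective that looks at products according to age, and the artefact is a step confined to the oldest children.

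**Working it through.** **Inputs from the documents.** Lying below 24 months, standing above (3.1.11). Entry at 6 to 23 months (3.1.2). Visits to month 6 (3.1.1). Index at months 0 and 3 only (3.1.11, Table 2). Detectable difference 0.4 SD, 5% alpha, 80% power, 25% loss, 12 groups of 134 (3.1.7).

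**Assumptions.** Ages evenly spread. Standing height below lying length by b = 0.3 to 1.0 cm. Index about 12 to 14 kg/m². Length 75 to 87 cm. SD of index change 0.5 to 1.0 kg/m². The documents give none of these for the trial sample.

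**1. The plan's own figures.** There is none for posture. The sample size reproduces: 16/0.4² = 100 per group; 100/0.75 = 133.3, so 134; 12 × 134 = 1608. At 100 per group, power for 0.4 SD is 80.7%.

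**2. Share of children who change posture by month m.** With U the upper age limit, share = (U − (24 − m))/(U − 6). The mean shift in length gain over all children is −b × share, shown here for U = 24.

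| | Month 3 | Month 6 |
|---|---|---|
| Share, U = 24 (under 24 months) | 3/18 = 16.7% | 6/18 = 33.3% |
| Share, U = 23.0 exactly | 2/17 = 11.8% | 5/17 = 29.4% |
| Share, linear age density, oldest end 0.25 to 2 times youngest (U = 24) | 8% to 21% | 20% to 41% |
| Mean shift, b = 0.3 cm | −0.3/6 = −0.05 cm | −0.3/3 = −0.10 cm |
| Mean shift, b = 1.0 cm | −1.0/6 = −0.17 cm | −1.0/3 = −0.33 cm |

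With U = 24 the shares are 268 and 536 of 1608 children, or 201 and 402 of the 1206 left after 25% loss.

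**3. Index of a child who changes posture (month 3).** Relative rise = (L/(L − b))² − 1.

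- Smallest: (87/86.7)² − 1 = 0.7%.
- Largest: (75/74)² − 1 = 2.7%.
- In kg/m²: 0.08 (0.7% of 12) to 0.38 (2.7% of 14).
- Averaged over all children at L = 80 cm and index 13 kg/m²: 0.10/6 = 0.02 to 0.33/6 = 0.06 kg/m².

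**4. Effect on a two-group comparison of the index.** Artefact SD = rise × √(1/6 × 5/6).

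- At b = 1.0 cm: 0.33 × 0.373 = 0.123 kg/m². The SE it contributes to a difference at 100 per group is 0.123 × √(2/100) = 0.017.
- At b = 0.3 cm: SD 0.037, SE 0.005.
- Adding this variance to an SD of 0.5 to 1.0 takes power from 80.7% to between 78.4% and 80.7%. The lowest value is for b = 1.0 cm and SD 0.5.

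For length gain the artefact SD at month 6 is b × √(1/3 × 2/3) = 0.14 to 0.47 cm. The documents give no SD of length gain, so no power figure follows.

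**5. What the age covariate removes.** If age enters linearly and is evenly spread, it explains 3p(1 − p) of the variance of a step with share p. At month 3 this is 3 × 1/6 × 5/6 = 42%; at month 6 it is 3 × 1/3 × 2/3 = 67%.

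**The case against.** The strongest reply is randomisation. Posture depends on age, and age is unrelated to allocation, so the artefact is equal across the 12 groups in expectation and cancels in product contrasts. Age is also a model covariate (section 3.1.13). This stands. A reader might infer that product effects are biased; the documents do not support that, either overall or within an age band. What remains for product contrasts is noise, and for the index it costs at most about 2 points of power.

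A reader might also carry the one-third figure over to the length-indexed outcome. That is wrong: the index exists only at months 0 and 3, so about one sixth of children are affected. Nor is one third a ceiling, since an older sample could exceed it.

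Two outcomes escape altogether. The primary outcome as written in section 3.1.5 is lean mass in kg and does not use length. Knee-heel length, taken by knemometer, does not use the lying/standing rule and gives a separate measure of linear growth. Both points stand.

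Finally, nothing here shows an error in WHZ. The protocol says that WHZ uses the WHO growth standard but not how posture is handled in deriving it, so the most one can say is that the derivation should be stated.

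The reply does not reach the absolute mean changes that the plan will present, or gains described by age. Randomisation does not remove a shift common to all groups from a group mean, and a linear age term does not remove a step.

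**Conclusion.** The point holds as a measurement inconsistency with limited consequences. Followed as written, the plan changes the measuring method within children who turn 24 months and states no correction.

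The shares affected are about 17% at month 3 and 33% at month 6 with even ages to under 24 months, or about 12% and 29% if the upper limit is exactly 23.0 months. The sizes rest on an assumed difference of 0.3 to 1.0 cm between postures and would scale with the true value. They apply to length gain, to outcomes divided by length, and to their description by age.

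Treatment comparisons remain valid, and the sample size needs no change on this ground. It is worth correcting because the bias is avoidable at almost no cost and touches both a named secondary outcome and the adopted expression of the primary one.

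**What to change.** In section 3.1.11, fix posture by enrolment and not by age at the visit: every participant is measured lying down at all visits to month 6 for length gain, kg/cm and fat-free mass index, and posture is recorded each time. Where a child is measured standing, apply one conversion, specified before analysis. Add a sensitivity analysis limited to children still under 24 months at the visit concerned. State separately that WHZ is derived with the posture convention of the growth standard used.

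If data have already been collected under the present rule, age at the visit identifies the children who changed posture, so the conversion and the sensitivity analysis are still possible.

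The cost is one line in the measuring procedure, a tick-box on the form and one sensitivity analysis. The downside is that lying measurement is less convenient for some two-year-olds.

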### **Physical activity assessment**

Data on physical activity will be collected at baseline and at 3 and 6 months. The measurement will be done using a high frequency accelerometer (Actigraph). This is a harmless electronic device, which is dust and waterproof, and placed on the body with an elastic belt. It has previously been used extensively for studying physical activity in adults, adolescents and children (*De Vries SI et al, 2006*), but very limited data is available on its use in small children (*Cliff DP et al, 2009*), and to our knowledge no studies have been conducted on children recovering from MAM in West Africa.

Therefore, prior to the main study, a pilot study was conducted to assess how the device is perceived and tolerated in this context. The pilot showed that the accelerometer was well accepted by children (20), mothers and the community and it was carried and returned after five days as instructed.

For the main study, the device will be placed on the waist of the child and should be carried at all times for 7 days at each assessment, to evaluate the level of everyday physical activity in the normal surroundings of the child. Children will be given a t-shirt to wear over the accelerometer. Upon completion of each measurement period the accelerometer will be taken off, and data transferred from the accelerometer into a computer for further analysis, using the actigraphy and management platform of Actigraph, ActiScience 5.

### **Tracer (Deuterium) dilution technique**

Body composition will be assessed at baseline and after 3 using the tracer dilution technique. In this technique, children will be weighed and a saliva sample will be collected with a cotton swab. Then, all children will be given a fixed standardized oral dose of liquid tracer (Deuterium, D2O), using 5 gr D2O diluted in 10 ml (~50% dilution) .. A second saliva sample will be taken after an equilibration time necessary for the tracer to evenly mix throughout the

body water. In healthy participants, equilibration is usually achieved after 2.5-4.5 hours and in general, children have faster water turnover than adults. However various disease states can influence water turnover and may delay equilibration (IAEA). Analysis of samples from the pilot study is ongoing and will determine the required equilibration time for children with MAM. During the equilibration time, children and caretakers will be provided with a meal and with activities (i.e knitting activities or others for the mothers and toys for the children). Health promotion sessions will also be conducted during this time.

The saliva sample will be analyzed for tracer distribution taking into account the volume of any fluid intake during the equilibration period. The concentration of the tracer in the saliva will allow estimating the total body water. Raw values for total body water will then be converted to lean mass measured in grams, using age-and sex-specific values for the hydration of lean tissue (Fomon SJ *et al*, 1982). The tracer enrichment of the saliva samples will be assessed using Fourier transform infrared (FTIR) spectrophotometry. Saliva samples will be analyzed at the IAEA Collaborating Centre, SJRI.

### **Child development**

Child development will be assessed in all children at baseline and after 3 and 6 months using a piloted and adapted version of the Malawi Developmental Assessment Tool (MDAT) (Gladstone *et al.*, 2010). The tool will focus on gross and fine motor development as well as language development and includes 30 milestones in each domain. Thus a total of 90 milestones

For the main study, testing of the child will take place in a quiet area. The child should be alert and well enough to be cooperative. If a child is too tired, irritable or sick to cooperate, the test will be postponed to the next fortnightly visit. The test will be carried out by trained health workers, in the presence of the mother/caretaker of the child. Health workers will evaluate each child starting with at least three milestones before the most age-appropriate milestone in each domain. . If the child passes these milestones, prior milestones will be rated as observed passed (10 points), Milestones will be rated with scores 10, 5 or 0. If the child can perform the milestone while being observed, the child will score 10. If the child cannot perform the milestone while being observed, but the mother reports that the child is able to perform the milestone at home, the child will score 5. If the child cannot perform the milestone and the mother reports that the child is not able to do so at home, the child will score 0.

After having failed six consecutive milestones in a domain (gross and fine motor or language), the assistant will move along to the next domain, following the same procedure.

After the evaluation, a total score will be calculated for each domain and an evaluation of the behaviour and cooperation of the child as well as the involvement of the mother will be carried out.

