### **Health and nutritional education**

Education on nutrition, health and hygiene will be provided in group sessions to all caretakers of eligible children on a regular basis. The content of nutrition education sessions will be based on locally available material, but adapted according to formative research carried out during the pilot study conducted in February 2013 where information of food availability and food consumption was collected.

In addition, caretakers of children allocated to the LNS and the iCSBS groups will receive specific recommendations according to the food to be taken by the child (frequency, timing, and, for the iCSBs groups, preparation and cooking).

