#### *3.1.9. Blinding*

This is an open trial since participants will not be blinded with respect to main type of food (LNS or iCSBs). However, within the arms with either iCSBs or LNS, participants will be blinded to the soy and milk content of the food. The investigator measuring the primary outcome (lean body-mass using tracer dilution) will be kept unaware of the allocation group and will therefore be blinded with respect to main type of food. In addition, the investigators measuring other biological factors, physical activity and milestones development will be blinded with respect to main type of food.

After baseline data have been collected, the child will be referred to the Supplement Responsible (SR). Only the SR will have access to the random sequence list.

For further information on the randomization and management of the experimental products, please see Standard Operating Procedure in annex 6

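### Blinding the assessor does not cover the mother-reported half credit in the milestone score, so the LNS-versus-iCSB comparison of motor and language development is open to reporting bias

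*Combined protocol and SAP*

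**What the plan says.** **Scoring (3.1.11, Child development).** The adapted tool "includes 30 milestones in each domain", for gross motor, fine motor and language development. On testing: "The test will be carried out by trained health workers, in the presence of the mother/caretaker of the child". On observed items: "If the child can perform the milestone while being observed, the child will score 10". If the milestone is not performed under observation "but the mother reports that the child is able to perform the milestone at home, the child will score 5", and it scores 0 if the mother says the child cannot do it at home either. A total is calculated for each domain. No score based on observed items alone is planned.

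**Start and stop rules (same section).** Testing begins at least three milestones below the most age-appropriate one. If those are passed, all earlier milestones are credited with 10 points each. "After having failed six consecutive milestones in a domain", the assessor moves to the next domain. The text does not say whether a 5 is a pass or a failure for either rule.

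**Blinding (3.1.9).** "participants will not be blinded with respect to main type of food (LNS or iCSBs"; within each food type they are blinded to soy and milk content. For assessors: "the investigators measuring other biological factors, physical activity and milestones development will be blinded with respect to main type of food". Section 3.1.14 rests control of observer bias on blinding the staff who assess outcomes, and does not list caretaker report as a limitation.

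**What the mother is told (3.1.3, Health and nutritional education).** "caretakers of children allocated to the LNS and the iCSBS groups will receive specific recommendations according to the food to be taken by the child".

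**Status.** Motor and language development is a secondary outcome (3.1.5). Secondary analyses carry no multiplicity adjustment (3.1.13).

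**The concern.** An assessor's blinding protects the judgements that the assessor makes. For a milestone attempted but not performed, the assessor makes no judgement between 5 and 0 and records what the mother says. She knows whether her child eats a ready-to-use paste or a cooked porridge. If mothers in one food type are, on average, readier to say that the child can do it at home, the domain means separate with no difference in development.

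At stake is the reading of any LNS-versus-iCSB difference in motor or language score at 3 or 6 months. The undefined status of a 5 adds to this. If a 5 can count as a pass among the starting milestones, reports can help to trigger 10-point credit for earlier items. If it does not count as a failure, reports lengthen the test and give more chances for observed passes. Either way, one report could move the total by more than its own 5 points.

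**Working it through.** **Who decides each part of the score**

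| Item | Points | Decided by | Knows LNS or iCSB? |
|---|---|---|---|
| Performed under observation | 10 | Assessor | No, per 3.1.9 |
| Attempted, not performed | 5 or 0 | Mother | Yes, per 3.1.9 |
| Before the starting set, if that set is passed | 10 | Rule; undefined if the set contains a 5 | Depends on the definition |
| After the six-failure stop | Not tested | Rule; undefined if the run contains a 5 | Depends on the definition |

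**When.** Under 3.1.9 the child goes to the person handling supplements only after baseline data are collected, so baseline reports precede knowledge of the food. Reports at 3 and 6 months follow it. Adjusting for baseline cannot remove a reporting difference that arises later.

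**Sample available.** The plan's own figure, for lean mass, reproduces: 16/0.4² = 100 per cell; 100/0.75 = 133.3, rounded up to 134; 12 × 134 = 1608. With six cells merged per food type, 6 × 100 = 600 evaluable children (6 × 134 × 0.75 = 603).

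**Size of one report.** A domain has 30 items and a maximum of 30 × 10 = 300 points. One reported item is 5/300 = 1.7% of that maximum.

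**Sensitivity calculation.** Two-sided 5% z test of two means, no true effect, one food type reporting *d* more items per child per domain:

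- standard error = √(2/600) = 0.0577 SD
- shift = 5*d*/SD
- chance of p<0.05 = P(|Z + shift/0.0577| > 1.96)

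Example with *d* = 0.5 and SD 20: shift = 2.5/20 = 0.125 SD; 0.125/0.0577 = 2.17; chance = 58%.

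The documents give no SD for the score and no value for *d*. Both are assumed.

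| Extra reported items per domain | Shift (points) | SD 20 | SD 30 | SD 40 | SD 60 |
|---|---|---|---|---|---|
| 0.1 | 0.5 | 7% | 6% | 6% | 5% |
| 0.5 | 2.5 | 58% | 30% | 19% | 11% |
| 1 | 5 | 99% | 82% | 58% | 30% |

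The significance threshold is 1.96 × 0.0577 = 0.113 SD. In items this is 0.113 × SD/5, or 0.45 items at SD 20 and 1.36 items at SD 60. The table counts only the direct 5 points and nothing that passes through the start or stop rule.

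**The case against.** A reader might infer that the plan's blinding claim for milestones is false. The documents do not support that. Section 3.1.9 claims blinding of the investigators who measure milestones, and section 3.1.14 of the outcome staff; neither claims it for the informant. The same paragraph of 3.1.9 declares the trial open as to food type. Both claims stay true when a mother answers a question. Her presence at the test creates a risk of disclosure to the assessor, but that is a separate matter.

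A reader might also infer that every milestone not seen by the assessor rests on her word. It does not: items before the starting set are credited by rule, and testing stops after six failures.

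Nor do the upper percentages predict anything. They need a small SD and a full extra item per domain. At 0.1 item the error rate is close to nominal. Both food types are newly developed supplements giving the same 500 kcal/day, there is no unsupplemented arm, and the documents give no reason why mothers should favour one food.

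The scope is narrow too. This is one of many secondary outcomes. The secondary soy and milk comparisons in 3.1.13, written for lean mass, are made within each food type, and an LNS-versus-iCSB milestone contrast is implied rather than spelled out. Children who cannot cooperate are tested at a later visit, and the mother's involvement is rated.

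All of this limits the point without removing it. Part of the score remains an unblinded report for one contrast, and the plan has no analysis that shows how far a difference depends on it.

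**Conclusion.** The concern holds in a limited form. Assessor blinding does not reach the mother-reported part of the milestone score, so the LNS-versus-iCSB comparison of motor and language scores at 3 and 6 months is open to reporting bias. The start and stop rules do not define how a 5 counts, so the effect of one report is not bounded at 5 points.

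The size cannot be determined from the documents. The 5% to 99% span in the table shows sensitivity to an assumed SD of 20 to 60 points and an assumed reporting difference of 0.1 to 1 item. It shows that a mean difference of about half an item to 1.4 items out of 30 would reach significance at this sample size. It does not show that such a difference will occur.

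**What to change.** 1. **Analysis (3.1.13).** Keep the 10/5/0 score as the main score. For every LNS-versus-iCSB comparison of a milestone domain, prespecify a sensitivity analysis on an observed-only score (observed pass = 10, otherwise 0). Attribute a difference to food type only if it is consistent on that score.
2. **Scoring rules (3.1.11, Child development).** Count a 5 as not passed in both the start and the stop rule. Reported credit then cannot add 10s for earlier items or lengthen the test. Without this, the observed-only score would still carry the mother's report indirectly.
3. **Blinding statement (3.1.9).** State that blinding to food type covers the assessor, not the mother's report.

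Making the observed-only score the main one for this contrast is not needed. It would displace the scoring of the piloted tool and give one outcome different main scores for different contrasts.

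The cost is a few sentences and one derived score, with no new data collection provided the item ratings are entered and not only the domain totals. The downside is that the observed-only score under-credits shy or tired children, which is a further reason to keep it as a sensitivity analysis.
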